#### Demographic and baseline information

During screening, different measures are made in order to get important initial values for the description of the study participants. Autistic symptoms are measured via self-report with the *Autism Spectrum Quotient* (AQ, [34]) and the *Empathy Quotient* (EQ, [35]). The authors of the AQ state that 80% of people within the autism spectrum obtain values of ≥32, while the values for non-autistic persons are < 32. The 50 items include questions on social skills, attention shifting, communication, attention to detail, and imagination. It is a questionnaire for self-report and is suitable for adults. The Cronbach’s alpha of the AQ for the overall sum score is .79. The EQ is used to differentiate between persons with ASD and non-autistic persons with regard to the dimension empathizing. The screening questionnaire comprises 40 items from which the EQ is calculated. Most non-autistic persons reach values of ≥30 whereas 80% of persons with ASD reach values < 30. The questionnaire is used for adults. The Cronbach’s alpha for the sum score is .92.

Alexithymia will be measured with the German version of the *Toronto-Alexithymia-Scale-26* (TAS -[25, 36]). It is used to measure emotional blindness (alexithymia) and is composed of three subscales: “Difficulties in identifying feelings,” “Difficulties in describing feelings,” and “Externally oriented thinking style.” An overall alexithymia score can be calculated from the three scales. The TAS-26 consists of 26 items and the overall scale has a Cronbach’s alpha of .81.

ADHD symptoms are assessed with the *Wender-Utah Rating Scale* (WURS-K, [37]) for symptoms in childhood (Cronbach’s alpha of .91) and with the *ADHD self-report* (ADHD, self-report, [38]) for current symptoms (Cronbach’s alpha between .70 and .90).

Intelligence will be measured with a culture fair test and the multiple choice vocabulary intelligence test. The *Culture Fair Intelligence Test*, second edition (CFT 20-R, [39]), measures the general intellectual level (basic intelligence) in terms of the “General Fluid Ability” according to Cattell (1963). This concept can be described as the ability to recognize figural relationships and formal-logical thinking problems with varying degrees of complexity and to process them within a certain time. The test is based on language-free and descriptive test tasks. The CFT 20-R consists of two similarly structured test parts, each with four subtests (series continuation, classifications, matrices and topological conclusions). The number of items in part 1 of the revised version was increased from 46 items to 57 items and was used to determine the IQ. The Cronbach’s alpha is .95.

The *Multiple choice vocabulary intelligence test* (German: Mehrfachwahl-Wortschatz Intelligenztest, MWT-B, [40]) is a very efficient test for measuring general intelligence levels that is frequently used in practice. The test mainly measures crystalline intelligence. It consists of 37 items, which are arranged in ascending order of difficulty.

The *NEO-Five-Factors-Inventory* (NEO-FFI, [41]) will be used to assess general personality traits by self-report. As the DSM personality interviews such as the Structured Clinical Interview for DSM-5 (SCID-5-PD, [42]) may lead to multiple diagnoses of personality disorders related to the high overlap of ASD symptoms, we considered a more general description of the personality to be more appropriate. The five factors of the personality questionnaire comprise neuroticism, extraversion, openness, conscientiousness, and agreeableness. Internal consistency (Cronbach’s alpha) of the five factors lies between .72 and .87.

The following *additional information about the participants* is collected: age, gender, native speaker, marital status, age and sex of siblings and own children, current life situation, school leaving certificate, education, profession, family members with ASD diagnosis, possible addiction-related Internet use in various areas, current psychiatric and psychotherapeutic treatments, time point and diagnostic center at ASD diagnosis, and years of therapeutic ASD treatment.

### Participant timeline {13}

The measurement points are displayed in Table 2.

**Table 2 Tab2:** T_F/S_ (treatment) = FASTER: 16 sessions at 120 min, group psychotherapy, 1/week and a single treatment at beginning and end of treatment; SCOTT&EVA: 32-h computer training with a minimum of 2 h/week, this will be controlled by online tracking and supervised training at the beginning of week one and ongoing once per month; B_F/S_ = Booster sessions FASTER: 4 sessions at 120 min 1/month; SCOTT&EVA: 4 sessions at 30 min 1/month. Screening-visits –t_2_ and –t_1_, t0, t1, t2 are measurements for all groups FASTER, SCOTT&EVA, and TAU

	Study period							
	Enrolment		Allocation					
Visit No./timepoint	SCR I −t_**2**_	SCR II −t_**1**_	t0		FASTER or SCOTT&EVA	t1		t2
Procedure	Screening				Treatment phase		Follow-up phase	
**Month**	**−2**	**−1**	**0**	**Randomization**	**1–4**	**4**	**5–8**	**8**
**Inclusion/exclusion criteria 1**	●							
**Inclusion/exclusion criteria 2**		●						
**Written informed consent**		●						
**Baseline (T0)**			●					
**Interventions**					T_F/S_			
**Post-treatment measurement (T1)**						●		
**Booster Sessions for treatments**							B_F/S_	
**Follow-up measurement (T2)**								●
**AE/SAE**			●		●	●	●	●
**Psychopharmacotherapy**	●	●	●		●	●	●	●

### Sample size {14}

The sample size calculation is based on the primary outcome measure “mean difference of the SRS-A score between baseline and 4 months after baseline”. The aim is to show that at least one of the two treatment protocols (SCOTT&EVA or FASTER) is superior to TAU which results in a union-intersection test. The sample size calculation is based on an ANCOVA model adjusted for the baseline SRS-A score. Since both models are well comparable, the power of the finally applied mixed model repeated measures (MMRM) is expected to be close to the intended value used for sample size calculation based on an ANCOVA. To obtain an estimate for the correlation between baseline and 4-months value, we analyzed internal data of 17 patients with a time difference of 9 months between measurements of SRS-A score. This yielded a correlation coefficient of .27 (95% CI [−.24; .66]). Hence, we use a conservative correlation of .2 for sample size calculation. The standardized treatment effects for SCOTT&EVA versus TAU and FASTER versus TAU are both assumed to be equal to 0.4. These prior assumptions are based on previous research results [43].

The global two-sided significance level is 0.05. The two test statistics referring to the comparison of TAU versus SCOTT&EVA and TAU versus FASTER are correlated due to the common comparator TAU. This correlation is determined by the ratio of variances of the group effect estimators. We assume equal variances in TAU and SCOTT&EVA and a small intra-group correlation of 0.05 in FASTER. Since SCOTT&EVA and TAU are no group therapies, we expect, if at all, a very small intra-group correlation caused by cluster randomization. Conservatively, we assume an intra-group correlation of 0.01 in these treatments. This results in a design effect of 1.25 inflating the variance in FASTER and a design effect of 1.05 inflating the variances in SCOTT&EVA and TAU. Hence, the correlation of test statistics is given by $$ \frac{1}{\sqrt{\left(1.05+1.05\right)\bullet \left(1.05+1.25\right)}}=0.455 $$. The correlation-adjusted local significance levels are computed from a bivariate normal distribution and are given by 0.026632 [44]. Applying these local levels guarantees that the family-wise error rate is controlled by the global two-sided significance level of 0.05.

The required sample size to find a significant effect in at least one of the two comparisons with a power of 0.8 under the above-described assumptions and at correlation-adjusted local levels of 0.026632 is given by 87 patients per group. Based on experiences in our previous FASTER and SCOTT&EVA trials, drop-out rates of about 20–25% are expected [13, 21]. Thus, we conservatively estimate the drop-out rate for the current study by 25% which compares well to similar interventions in adult ASD [43, 45]. To obtain a sample size that can be divided by the cluster size of 6, 120 patients for each group will be required to be randomized resulting in a total sample size of 360.

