#### Analysis

Let μ denote the unknown true mean difference of the SRS-A score between baseline and 4 months after baseline. The following two primary local test problems are assessed:
$$ {\mathrm{H}}_{0,\mathrm{SCOTT}\&\mathrm{EVA}}:{\upmu}_{\mathrm{SCOTT}\&\mathrm{EVA}}={\upmu}_{\mathrm{TAU}}\ \mathrm{versus}\ {\mathrm{H}}_1:{\upmu}_{\mathrm{SCOTT}\&\mathrm{EVA}}\ne {\upmu}_{\mathrm{TAU}} $$

and
$$ {\mathrm{H}}_{0,\mathrm{FASTER}}:{\upmu}_{\mathrm{FASTER}}={\upmu}_{\mathrm{TAU}}\ \mathrm{versus}\ {\mathrm{H}}_1:{\upmu}_{\mathrm{FASTER}}\ne {\upmu}_{\mathrm{TAU}} $$

The aim is to show that at least one of the two local alternative hypotheses holds true. For each pairwise comparison (TAU versus FASTER and TAU versus SCOTT&EVA) a Mixed Model Repeated Measures (MMRM) will be applied. It includes the difference of the SRS-A score between baseline and 4 months after baseline as the dependent variable, the baseline SRS-A score, and the group allocation as fixed effects, and the center and the cluster as random effects. The MMRM uses all available changes from baseline SRS-A score for all patients for model estimation. In the “Sample size {14}” section, the local significance level of .026632 has been deduced. In case that at least one of the null hypotheses specified above can be rejected at the local significance levels of .026632, we hierarchically assess additionally the following test problem:
$$ {\mathrm{H}}_{0,\mathrm{SCOFA}}:{\upmu}_{\mathrm{SCOTT}\&\mathrm{EVA}}={\upmu}_{\mathrm{FASTER}}\ \mathrm{versus}\ {\mathrm{H}}_1:{\upmu}_{\mathrm{SCOTT}\&\mathrm{EVA}}\ne {\upmu}_{\mathrm{FASTER}} $$

at the full two-sided level of 0.05 in a confirmatory manner. In case neither H0, SCOTT&EVA nor H0, FASTER can be rejected, the comparison between the FASTER and the SCOTT&EVA arm is done descriptively. The confirmatory analysis of the primary efficacy endpoint corresponds to the primary estimand and will be conducted in the full analysis set.

As a sensitivity analysis to the primary efficacy analysis, corresponding MMRMs with additional covariates/factors given by IQ, age, gender, ASD symptom severity, MET test result, and center will be conducted. Furthermore, the separate items of the SRS-A score are analyzed individually to investigate which items differ between the treatment groups. Details of these analyses will be specified in the statistical analysis plan (SAP).

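### The correlation behind the local significance level uses 1 instead of the TAU design effect 1.05 in its numerator: a minor arithmetic error that is conservative and leaves 360 patients unchanged

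*Protocol article*

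**What the plan says.** All statements are in the protocol article.

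- Sample size {14}, error rate and aim: "The global two-sided significance level is 0.05". The aim is to show that at least one intervention is "superior to TAU which results in a union-intersection test".
- Sample size {14}, source of the correlation: the two test statistics "are correlated due to the common comparator TAU", and their correlation is said to follow from the variances of the group effect estimators.
- Sample size {14}, clustering: the plan assumes "a small intra-group correlation of 0.05 in FASTER" and 0.01 in SCOTT&EVA and TAU. It turns these into design effects of 1.25 for FASTER and 1.05 for the other two arms.
- Sample size {14}, correlation: "Hence, the correlation of test statistics is given by" 1/√((1.05+1.05)(1.05+1.25)) = 0.455.
- Sample size {14}, results: "The correlation-adjusted local significance levels are computed from a bivariate normal distribution and are given by 0.026632". The number needed for 80% power "at correlation-adjusted local levels of 0.026632 is given by 87 patients per group". After 25% drop-out and rounding to the cluster size of 6, this becomes 120 per group and 360 in total.
- Analysis: the section refers back, saying that "the local significance level of .026632 has been deduced". It uses that level as the threshold for both primary tests and as the gate to the confirmatory comparison of FASTER with SCOTT&EVA.
- Discussion: 87 per group is repeated as the required number.

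**The concern.** Within one fraction the TAU variance takes two values: 1.05 in each bracket of the denominator and 1 in the numerator. The plan's own design effects therefore do not give the printed correlation. That correlation fixes the local level and, with it, the required number per group, so any error there carries into the pre-specified decision rule for the primary endpoint and into the stated sample size.

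Three things could be at stake: whether the family-wise error stays within 0.05, whether 87 per group gives the stated power, and whether 360 patients are enough. A p-value between 0.02663 and 0.02679 would be judged differently under the two levels, and a threshold cannot credibly be changed once the results are known.

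**Working it through.** **Inputs (all from the protocol).** Global two-sided level 0.05; design effects 1.05 (TAU), 1.05 (SCOTT&EVA) and 1.25 (FASTER), which follow from 1 + (6 − 1) × ICC with ICC 0.01, 0.01 and 0.05; standardized effect 0.4 in both comparisons; baseline-to-follow-up correlation 0.2; power 0.80 for at least one significant comparison; allocation 1:1:1; drop-out 25%; cluster size 6.

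**1. Reproduce the plan's figures.**

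- Correlation as printed: 1/√(2.10 × 2.30) = 0.4550.
- Local level: solve P(|Z1| > c or |Z2| > c) = 0.05 for a bivariate normal with that correlation. This gives 0.026633, against the stated 0.026632. (Doubling the one-sided 0.025 solution gives 0.0266317, which rounds to the stated figure.)
- Sample size: each Z has mean 0.4/SE, with SE² = (1 − 0.2²)(DE_TAU + DE_treatment)/n = 0.96 × 2.10/n for SCOTT&EVA and 0.96 × 2.30/n for FASTER. The power to reject at least once is 0.797 at n = 86 and 0.8015 at n = 87, so the plan's 87 is reproduced.

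The numerator of 1 was therefore used in the actual calculation. It is not a printing or extraction fault.

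**2. Derive the correlation.** With independent arms of equal size, and on the scale of the design effects:

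- Cov(SCOTT&EVA − TAU, FASTER − TAU) = Var(TAU mean) = 1.05
- Var(SCOTT&EVA − TAU) = 1.05 + 1.05 = 2.10
- Var(FASTER − TAU) = 1.05 + 1.25 = 2.30
- Correlation = 1.05/√(2.10 × 2.30) = 0.4778

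**3. Carry the corrected correlation through.**

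| Quantity | As stated (r = 0.455) | r = 0.478, level kept at 0.026632 | r = 0.478, level recomputed |
|---|---|---|---|
| Local level | 0.026632 | 0.026632 | 0.02679 |
| Critical z | 2.2169 | 2.2169 | 2.2146 |
| Family-wise error | 0.0500 | 0.0497 | 0.0500 |
| Power at 87 per group | 0.8015 | 0.7978 | 0.7985 |
| Power at 88 per group | 0.806 | 0.802 | 0.803 |
| Smallest n with power of at least 0.80 | 87 | 88 | 88 |

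**4. Randomized number.** 88/0.75 = 117.3, so 118, and 120 as the next multiple of 6. The total remains 3 × 120 = 360. With 25% drop-out, 120 leaves 90 evaluable per group. At 90 and the corrected correlation, power is 0.811 with the stated level and 0.812 with the recomputed one.

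**The case against.** The strongest defence is that nothing the trial does goes wrong. A pre-specified level slightly below the exact one is a valid confirmatory rule. At 0.026632 the family-wise error is 0.0497, the two critical values differ by only 0.0023, power at 87 still rounds to 0.80, and the 90 evaluable patients expected per group give about 0.81. This stands, and it makes the point minor.

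A second defence is that 0.02679 is no firmer than the figure it replaces, because both depend on assumed ICCs. As an illustration outside the plan, a FASTER ICC of 0.10 (design effect 1.5) gives 1.05/√(2.10 × 2.55) = 0.454 and a local level of 0.026624, almost exactly the stated one. This also stands, and it is a good reason to allow 0.026632 to be kept. It does not rescue the derivation, since the protocol fixes the ICC at 0.05 and the figures it prints do not follow from that.

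A reader might infer that the primary tests have an inflated type I error, or that the trial is underpowered. The documents support neither: under the plan's assumptions the slip is conservative for the error rate, and rounding up to 120 per group absorbs the one extra patient. A reader might also conclude that the pairwise models must give way to one three-arm model with Dunnett-type adjusted p-values. That is a different analysis strategy and is not needed to correct this error.

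**Conclusion.** The formula is wrong as written. On the protocol's own inputs the correlation is 0.478, not 0.455; the exact local level is 0.02679, not 0.026632; and the required number is 88 per group, not 87. The shift is about 0.00016 in the level, one patient per group, and 0.2 percentage points below the 80% target at 87.

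The protocol's claim that the family-wise error stays within 0.05 survives, with about 0.0003 unspent. The randomized 120 per group and 360 in total are unaffected.

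These figures rest on the stated ICCs, equal evaluable numbers per arm, independent arms, a normal approximation, and the ANCOVA variance factor 1 − 0.2² = 0.96. The last two reproduce the plan's own 87. The point deserves correction because the constant is the decision rule for both primary hypotheses, not because the trial's conclusions are in danger.

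**What to change.** Before unblinding:

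1. In Sample size {14}, put 1.05 in the numerator and give the correlation as 0.478.
2. Either state the local level as 0.02679, or keep 0.026632 and add that it is slightly conservative (family-wise error 0.0497 under the planning assumptions). Use the same choice in Sample size {14} and in Analysis.
3. Restate 87 as 88 per group in Sample size {14} and in the Discussion. Keep 120 per group and 360 in total.

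The cost is the correction of a few printed figures. Recruitment, randomization and the analysis model do not change. Adjusted p-values from a single three-arm model remain an option for the sponsor but are not part of this correction.

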### Recruitment {15}

Participant recruitment is expected to begin in March 2021 and will continue for 28 months.

Each of the participating centers has consented to include a certain number of patients according to their usual quantities of diagnostics and treatment of autistic patients. The study centers keep waitlists for diagnostics and treatment and will also use existing patient files for screening. Flyers with cover letters for medical practices and autism centers as well as press information have been prepared with general information about the study. These materials can be adapted with each study center’s contact information and distributed within their local networks. Some of the study centers have well-established web pages in place to advertise clinical trials especially for their autistic patients. In addition, Germany’s largest society for autistic people and their caregivers, Autismus Deutschland e.V., has been requested to include information about the study on their webpage for advertising trials looking for autistic participants in the German speaking area.

## Assignment of interventions: allocation

### Sequence generation {16a}

Subjects are randomized by cluster randomization in an allocation ratio of 1:1:1. The cluster size is set to 6 patients per cluster. This means that groups of 6 participants are built within each center, and these groups are randomly assigned to one of the three study arms. The randomization will not be stratified by center or other factors. An Internet-based randomization system (http://www.randomizer.at) will be used and the allocation sequence is created by computer-generated random numbers.

All transactions will be logged. The software’s GCP-compliance has been confirmed by the Austrian Federal Office for Safety in Health Care (BASG). Details of the randomization scheme will be specified in an external document accessible to the Institute of Medical Biometry and Informatics (IMBI, Heidelberg) only to minimize selection bias.

### Concealment mechanism {16b}

The allocation sequence is implemented and concealed by the randomization tool “randomizer” (http://www.randomizer.at). Study staff which do not have to be blind will insert always six in the study included study participants’ identification codes into the randomizer online. All already randomized groups can be viewed by the study staff of the corresponding center and from the IMBI. Subjects withdrawn from the trial will retain their identification codes (e.g., randomization number, if already given). New subjects must always be allotted a new identification code.

### Implementation {16c}

The study-specific randomization tool of http://www.randomizer.at will be set up by the Institute of Medical Biometry and Informatics (IMBI, Heidelberg). All study participants who give written consent and meet the eligibility criteria will be randomized in clusters. Raters from each center decide on the inclusion of potential study participants based on clearly defined criteria. Randomization will be requested from the rater of each study center via the online randomization tool “randomizer.at” from the University of Graz, Austria. Only the data manager of the Institute of Medical Biometry and Informatics (IMBI, Heidelberg) has complete access to the stratification and randomization process. All centers add six new participant identification numbers into the randomizer for a complete cluster and will then receive the random allocation to one of the three groups (group therapy FASTER, web-based training SCOTT&EVA or TAU).

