## Assignment of interventions: blinding

### Who will be blinded {17a}

Randomization takes place after baseline. Study staff from each study center who measure post-treatment (T1) and follow-up (T2) are blinded regarding group assignment. Rater and therapy rooms are far apart, to support the blinding of the raters throughout the whole course of the study. Raters log at the measurement time points T1 and T2 for each study participant whether they are blinded or not. Due to study design and significantly different interventions in the study arms, therapists, study participants, and additional persons who are responsible for the external assessment for social responsiveness are not blinded. The biometrician and his representative will remain blinded until data base closure.

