### Procedure for unblinding if needed {17b}

No procedure for unblinding of therapists is necessary. Therapists always have information about the allocation of each study participant. If unblinding of raters takes place by accident, the unblinding is recorded and another rater will perform the future measurements (T1 or T2).

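### The Implementation section has the center's rater request randomization, against the Concealment section and the requirement that T1/T2 raters be blinded

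*Protocol article*

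**What the plan says.** Two adjacent sections of the protocol article describe who operates randomization.

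- Concealment mechanism {16b}: "Study staff which do not have to be blind will insert always six in the study included study participants" (the sentence goes on to their identification codes, which are entered in the online randomizer). The same section adds: "All already randomized groups can be viewed by the study staff of the corresponding center and from the IMBI".
- Implementation {16c}: "Raters from each center decide on the inclusion of potential study participants based on clearly defined criteria". Then: "Randomization will be requested from the rater of each study center via the online randomization tool". Centers enter six new identification numbers for a complete cluster and "will then receive the random allocation to one of the three groups".

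Three other places set the blinding that these steps must respect.

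- Who will be blinded {17a}: "Study staff from each study center who measure post-treatment (T1) and follow-up (T2) are blinded regarding group assignment". Rating and therapy rooms are kept apart "to support the blinding of the raters throughout the whole course of the study", and raters log at T1 and T2 whether they are still blind. Participants, therapists and the informants who complete the SRS-A are not blinded.
- Procedure for unblinding if needed {17b}: "If unblinding of raters takes place by accident, the unblinding is recorded and another rater will perform the future measurements".
- The Discussion says that the data collectors at each center are blinded, kept apart from intervention work, and unaware of individual allocation.

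**The concern.** Taken literally, Implementation {16c} makes the rater a party to the step that reveals the arm, and it reveals the arm for six participants at once. The section just before it gives that step to staff who need not be blind. The right to view randomized groups is a second route to the same knowledge, because it is granted to the center's study staff and raters are not excluded.

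Trial design {8} calls the study observer-blinded. Since participants, therapists and SRS-A informants all know the arm, the center's raters are the only blinded outcome assessors. What is at stake is the credibility of what those raters assess at T1 and T2, and whether the label is accurate. Once a rater has learned the arm, that knowledge cannot be withdrawn.

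**Working it through.** No arithmetic applies. The sample size (87 per group, 360 in total) and the local significance level of 0.026632 do not depend on who operates the randomizer. The check is a comparison of the sections.

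1. **Who uses the tool.** {16b} says staff who do not have to be blind. {16c} says the rater. The preposition in {16c} is odd, and the sentence probably means that the rater makes the request. On either reading the rater takes part in the request, and the request runs through the tool.

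2. **Who learns the arm.** {16c} says the centers receive it after entering the six numbers. It does not say that the rater personally receives it. That is a short inference: whoever uses the tool sees what it returns.

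3. **Who can look it up later.** {16b} gives the center's study staff and the IMBI a view of all randomized groups. Raters are study staff of the center. No restriction is stated.

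4. **Whether the requesting rater may be unblinded.** The direct duty in {17a} falls on staff who measure T1 and T2, and randomization follows baseline. An enrolling rater who never assessed T1 or T2 could therefore know the arm without breaching that sentence. However, no section creates such a separate role. Strategies to improve adherence to interventions {11c} describes one rater role spanning screening, baseline, post-treatment and follow-up. {17a} also speaks of blinding raters over the whole study, and the Discussion describes the rating staff as a body as unaware of allocation.

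5. **Whether the unblinding rule repairs it.** {17b} covers accidental unblinding. Knowledge gained by following {16c}, or through the view granted in {16b}, is not an accident, so the rule does not clearly apply.

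6. **What is exposed.**
   - *Primary outcome:* the SRS-A completed by a parent, spouse or other person, who is unblinded by design. The rater's knowledge does not change who gives that rating.
   - *GAF at T1 and T2:* a staff judgement, and therefore open to expectation. This is the main exposure.
   - *MET at T1 and T2:* a computer test that the protocol describes as objective. Only its administration could be influenced.
   - *Most other T1/T2 measures:* questionnaires, and so not rated by staff.

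Steps 1 and 3 conflict with {17a} and the Discussion. Step 4 shows that the document offers no arrangement that removes the conflict, and step 6 limits the consequence to a small part of the outcome set.

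**The case against.** The strongest reply is that the intent is clear and one sentence is badly worded. {16b}, {17a}, {17b} and the Discussion all point to unblinded staff randomizing and blinded staff assessing. The sentence in {16c} can be read as the rater, having decided on inclusion, asking for randomization while someone else operates the tool. A different person may then rate T1 and T2; {17b} presupposes that another rater is available, and {11c} is a statement about training, not a rule that one person covers every visit. Raters also log their blinding status, so a failure would be recorded.

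Much of this stands. Receipt of the arm by the rater is inferred, and the harm depends on staffing that the document does not describe. But the milder reading of {16c} fits poorly with a request made through the online tool, and it leaves the open view of randomized groups untouched. Logging records a loss of blinding without preventing it.

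A reader might go further in three ways that the document does not support.

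- *That this removes the only blinding in the trial.* {17a} also keeps the biometrician and a representative blinded until the database is closed. The narrower statement, that raters are the only blinded outcome assessors, is correct.
- *That the replacement rule would be set off by every cluster.* {17b} is limited to accidents. If another rater did take over, the later ratings would not be unblinded.
- *That all participants' T1 and T2 ratings, or an equal share per center, are unblinded.* This would need the requesting rater to assess T1 and T2 at every center, with no drop-out and equal recruitment. The protocol plans for 25% drop-out, and Recruitment {15} lets centers agree different numbers.

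**Conclusion.** The point holds as an inconsistency in assigned roles that could defeat assessor blinding if the text were followed as written. The sections must be reconciled.

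Its effect is confined to staff-assessed secondary outcomes at T1 and T2, chiefly the GAF and to a lesser degree MET administration, and to the observer-blinded description. Secondary outcomes are analysed descriptively. The primary SRS-A endpoint, the confirmatory tests, the significance levels and the sample size are unaffected, and it would be wrong to read this point as a threat to the primary result.

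The consequence rests on two assumptions: that whoever requests randomization sees the result, or that raters use the viewing right; and that this person also assesses T1 or T2. The document excludes neither. How many ratings would be affected cannot be stated, because staffing per center is not given. This is a should-fix correction.

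**What to change.** In Implementation {16c}, replace the rater as requester with a named unblinded role that performs no ratings, in line with Concealment mechanism {16b}. State that raters report only that a participant is eligible and that T0 is complete.

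In {16b}, restrict the view of randomized groups to the center's unblinded staff, expressly excluding anyone who rates T1 or T2, and to those IMBI roles that need it. That limit should respect the blinding of the biometrician and representative in {17a}.

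The cost is a sentence or two in the protocol and a change of user rights in the randomization tool. Sample size, analysis and visit schedule stay as they are. It should be in place before the first cluster is randomized.
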